### Measurement and outcomes

For the effectiveness trial, data come from 3 sources: (1) youth self-report at Months 0, 3, 6, 12, and 18; monthly post-release check-ins, (2) JJ facility records (e.g., recidivism, treatment utilization), and (3) caregiver self-report with a timeframe identical to youth. Table 4 depicts research goals, assessment instruments, data collection timeline, and youth and/or caregiver single or dyadic perspective on each construct. The primary outcome is *days to youth initiation* of non-medical opioid use: measured by (a) Timeline Followback [51], (b) TCU Drug Screen 5 with Opioid Supplement (TCU DS 5-OS) [52], and (c) Substance Use Involvement items from the HEAL Prevention Cooperative [53]. Secondary outcomes include putative change mechanisms, public health, and public safety outcomes. Putative change mechanisms include youth self-regulation and self-efficacy (e.g., “How confident are you that you will not misuse a prescription opioid in the next 30 days”) [53] and youth/caregiver psychosocial functioning and relationships between youth and caregivers. Self-regulation is measured with the TCU Adolescent Thinking forms on regulation (TCU THK-NUY, TCU THK-PUY; decisions influenced by positive or negative emotion) [54], supplemented with the delayed discounting task (DD task) [55], Difficulties in Emotion Regulation Scale (DERS) [56], and Barkley Deficits in Executive Functioning Scale-CA Short Form (BDEFS-CA) [57]. *Psychosocial functioning* is measured by the Strengths and Difficulties Questionnaire for youth (SDQ) [58], Generalized Anxiety Disorder Assessment (GAD-7) [59], Patient Health Questionnaire (PHQ-8) [60], PROMIS-Pain [61], and items that evaluate youth’s self-reported efficacy to resist opioids (“How confident are you that you will not misuse a prescription opioid in the next 30 days?”) [53]. *Youth/caregiver relationships* are measured using the Family Assessment Device (FAD) [62], the Experiences in Close Relationships – Relationship Structures (ECR-RS) [63], and the Attachment, Relational Frustration, and Discipline Practices scales from the Behavior Assessment System for Children Parent Relational Questionnaire (BASC-3) [64].

**Table 4 Tab4:** An overview of assessment and timeline for the effectiveness of TBRI intervention

Construct and Instrument	Measurement Time Points						Participant	
	Baseline	MO 3	MO 6	MO 12	MO 18	Monthly check-in	Youth	Caregiver
Youth SU								
TLFB		x	x	x	x		x	
TCU DS 5 - OS	x	x	x	x	x		x	
HEAL SU Involvement	x	x	x	x	x		x	
Monthly check-in						x	x	
JJ records	Administrative records (Years 2–5)						NA	NA
Youth Self-regulation								
TCU THK, NUY and PUY	x		x	x			x	
DD task	x	x		x			x	
DERS	x	x	x	x	x		x	
BDEFS-CA	x		x	x				x
SDQ	x		x		x		x	x
GAD	x	x	x	x	x		x	x
PHQ-8	x	x	x	x	x		x	x
PROMIS Pain	x	x	x	x	x		x	x
Self-efficacy	x	x	x	x			x	
Monthly check-in						x	x	
Youth/Safe Adult Relationship								
FAD	x	x	x		x		x	x
ECR– RS	x	x		x	x		x	x
BASC-3	x		x	x				x
Monthly check-in						x	x	
Public Health and Safety								
Opioid-related health	x	x	x	x	x		x	x
JJ records	Administrative records (Years 2–5)						NA	NA
Family Background								
Background	x						x	x
TCU DS 5- OS	x							x
ACEs	x						x	x
Social SU exposure	x	x	x	x	x		x	
Parenting								
PMI	x	x						x
CGSQ-SF	x	x	x					x
RS	x							x
Service utilization		x	x	x	x		x	x
COVID-19 impact	x	x	x	x	x		x	x
Utilization of TBRI Principles								
Utilization and Importance		x	x	x	x			x
CAWS	Administered at end of TBRI Group Training and In-Home Training							
Intervention fidelity	Administered at post-TBRI session						x	x

Note: TLFB = Timeline Followback, TCU DS 5-OS = TCU Drug Screen 5 with Opioid Supplement, HEAL SU Involvement = Substance Use Involvement items from the HEAL Prevention Cooperative, TCU THK- NUY and PUY = TCU Adolescent Thinking Forms-Negative and Positive Urgency Scales, DD task = Delayed Discounting Task, DERS = Difficulties in Emotion Regulation Scale, BDEFS-CA = Barkley Deficits in Executive Functioning Scale -CA Short Form, SDQ = Strengths and Difficulties Questionnaire, GAD-7 = Generalized Anxiety Disorder Assessment, PHQ-8 = Patient Health Questionnaire, Self-Efficacy = Self-Efficacy to Avoid Opioids, FAD = Family Assessment Device, ECR-RS = Experiences in Close Relationships – Relationship Structures, BASC-3 = Behavior Assessment System for Children- Parent Relational Questionnaire, ACEs = Adverse Childhood Experiences, PMI = Parent Motivation Inventory, CGSQ-SF = Caregiver Strain Questionnaire- Revised Short Form, RS = Resiliency of Self-Efficacy Scale, Utilization and Importance of TBRI = Perceived Importance and Use of TBRI Strategies, CAWS = Child and Adolescent Well-being Scale; at MO 3, only the Affective Responsiveness scale from the FAD will be administered; at each time point, only the Attachment, Relational Frustration, and Discipline Practices scales from the BASC-3 will be administered; for baseline the trait version of DERS will be administered and for all follow-ups the state version of DERS will be administered; CAWS and Intervention Fidelity will both be reported by TBRI Practitioners; Baseline = initial assessment, MO 3 = 3 month follow-up, MO 6 = 6 month follow-up, MO 12 = 12 month follow-up, MO 18 = 18 month follow-up

*Public health and safety outcomes* include opioid-related health, opioid use overdose, use of other illegal substances, recidivism, and SU or MH treatment records. *Opioid-related health* outcomes include SU treatment, hospital visits related to SU, diagnosis, overdose, and receipt of Narcan [65]. *Recidivism* information (re-arrest, re-adjudication), urinalysis results, and *treatment* records (type of referral, service receipt) come from JJ facility youth records [65]. For these data, sharing agreements between each state-level JJ facility and the research institute are established, specifying how de-identified records are shared, stored, and analyzed, following models from previous collaborations [66]. *Background information* on youth is extracted from existing JJ youth records (e.g., offense, disposition decision, supervision level, offense history including truancy, and prior SU or MH diagnosis).

Youth and caregivers provide different pieces of background information that serve as covariates or moderators, including demographics (e.g., age, sex, race/ethnicity, employment, education). Caregivers are also asked about their SU (TCU DS 5-OS) [52] and relationship with their own caregiver using the Experiences in Close Relationships-Relationship Structures (ECR-RS) [63]. Other potential covariates include number and type of ACEs [67], youth self-reported social exposure to substance use (e.g., “How often does the adult who is most important to you drink alcohol?”) [53], services youth and family received (adapted from the Child and Adolescent Services Assessment) [68], caregiver motivation in treatment participation (Parent Motivation Inventory; PMI) [69], parenting strain (Caregiver Strain Questionnaire-Revised Short Form; CGSQ-SF) [70], and parental resiliency (Resiliency of Self-Efficacy Scale; RS) [71]. Participants are also asked to respond to two open-ended questions regarding the impact of COVID-19 (e.g., “How is the COVID-19 crisis affecting you or has affected you?”). *Monthly phone check-ins* with youth assess 8 indicators of any opioid use; any alcohol, other drug use; truancy; trouble with the law, increases in depression, increases in anxiety, increases in the stress in relationship with the safe adult in the past month.

Participants in the SRP + TBRI cohort are asked to report on the utilization of intervention content and intervention fidelity, which are developed specifically for this project. Caregivers’ use of TBRI strategies is assessed by (1) self-report after completion of final TBRI Group Training session and after each TBRI In-Home Training session and (2) RA report upon completion of each TBRI Nurture Group and TBRI In-Home Training sessions. RAs and participants complete a post-session checklist after each session to assess fidelity of content delivery and participant engagement.

For the implementation assessment, the LeSA JJ staff survey (see Table 5 for a description and timeline) includes information on organizational context (Survey for Juvenile Justice Secure Facilities) [72], staff characteristics (Survey of Organizational Functioning and Leadership, Professional Quality of Life; SOFL, PQL) [73], use of trauma-informed care (Attitudes Related to Trauma-Informed Care Scale; ARTIC) [74], use of TBRI intervention strategies (TBRI Acceptability, Appropriateness, and Feasibility scale), and TBRI Professional Use scale [75], and answer two open-ended questions regarding the impact of COVID-19. Youth participating in LeSA also report their perceived social support from facility staff (with the Berlin Social Support Scale; BSSS) [76]. During focus groups, staff report routine practices in the use of trauma-informed approaches (e.g., “How does your facility address issues that youth may have had due to their traumatic experience(s)?”) and child-centered strategies (e.g., “In what ways does your agency strive to meet the unique needs of youth?”), agency facilitators/barriers to uptake of new interventions (e.g., “What (if any) changes have you made that produced significant changes for youth?”), general penetration of TBRI within the agency (e.g., “What (if any) changes have you made using TBRI that produced significant changes for the staff or your organization more broadly?”), and agency interest/success in sustaining and/or expanding TBRI practices (e.g., “Are you planning to continue TBRI practices at your agency?”). The focus groups will be held once per year over 4 years for approximately 60 min.

**Table 5 Tab5:** An overview of assessment and timeline for the implementation

Construct and Instrument	Brief Description	Measurement Time Points				Participant
		Start of Baseline or New Recruitment	Start of Staff TBRI Training	End of Staff TBRI Training or Start of Follow-up	End of Follow-up	
Survey for Juvenile Justice Secure Facilities	Agency and youth characteristics, staffing, clinical assessment, behavioral, treatment services, family engagement.	x	x	x	x	Agency administrator or designated representative
Staff Background	Staff age, race, ethnicity, education, work experiences.	x				All JJ staff
SOFL, PQL	Climate and staff characteristics.	x	x	x	x	All JJ staff
ACEs	Staff ACEs	x				All JJ staff
ARTIC	Attitudes toward trauma-informed care.	x	x	x	x	All JJ staff
TBRI Acceptability, Appropriateness, and Feasibility	Staff attitudes toward TBR		x	x	x	All JJ staff
TBRI Professional Use	Staff use of TBRI strategies.	x	x	x	x	All JJ staff
COVID-19 Impact	COVID-19 impact on staff, work environment, and services for youth.	x	x	x	x	All JJ staff
JJ Staff Focus Group	Use of trauma-informed strategies, facilitators and barriers to uptake of new interventions, use of TBRI, agency interest/success in sustaining and/or expanding TBRI practices.	x	x	x	x	Leadership and line staff, separately.

Note: SOFL = Survey of Organizational Functioning, PQL = Professional Quality of Life, ACEs = Adverse Childhood Experiences, ARTIC = Attitudes Related to Trauma-Informed Care, BSSS = Berlin Social Support Scale

For economic analyses, the Drug Abuse Treatment Cost Analysis Program (DATCAP) [77, 78] is used to capture implementation and operating costs of TBRI [79] [78], generating cost summary statistics using data on intervention engagement and youth case flow (e.g., the average annual cost per youth; average cost per treatment episode per youth) [80] [81].

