## Methods/design

### Research aims

The specific aims of the LeSA Project are to: (1) test the effectiveness of the TBRI intervention and its different support formats – no in-home TBRI support, Structured Coaching, Responsive Coaching – on (a) preventing initiation and/or escalation of opioid use, (b) public health and public safety outcomes, (c) putative change mechanisms, including self-regulation, psychosocial functioning, and relationship with a safe adult; (2) document factors related to TBRI implementation and sustainment; and (3) estimate the start-up and implementation costs and cost-effectiveness of TBRI support options relative to standard re-entry practices in achieving lower rates of opioid initiation and reductions in healthcare and JJ system costs.

Primary hypotheses are as follows:
H1: Compared to youth receiving Standard Re-entry Practices (SRP) only, youth receiving TBRI in addition to SRP are less likely to initiate opioid use following discharge.H2: Compared to no in-home TBRI support, youth receiving Structured or Responsive Coaching are less likely to initiate opioid use following discharge, with the longest time to initiation occurring among youth receiving Responsive Coaching.H3: TBRI is most effective for preventing opioid initiation when facilities routinely use TBRI strategies within their residential settings, given increases in continuity as the youth transitions home from residential care.H4: The cost of implementing TBRI + SRP is higher than SRP alone, with higher cost-effectiveness when TBRI is added.

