### Study samples and recruitment

A total of nine residential facilities designed to address the behavioral and emotional needs of justice-involved youth serve as research sites for this project. Three are located in a Midwestern state and 6 in a Southwestern state in the U.S.A. Three are operated by the state JJ system, 4 by local JJ departments, and 2 by an independent agency. All sites are secure residential programs with medium security protocols, all receive referrals from JJ departments across a wide geographic region, and all provide educational, medical, and behavioral health services. At project start, 3 sites had incorporated TBRI into their trauma-informed care approach for 1–3 years, 2 were familiar with TBRI but not using principles and strategies, and 4 were unfamiliar with TBRI.

The project involves two target samples drawn from the nine facilities at rates proportional to current census/staffing levels. The effectiveness trial sample includes a total of 360 youth/caregiver (e.g., parent/guardian, extended family member) dyads recruited from participating JJ facilities over a 3-year period (approximately 10–15 dyads/year per site). Inclusion criteria include youth ages 15–18 at study enrollment who (a) are disposed to community supervision (i.e., probation) and receiving care in a secure JJ facility, (b) have no indication of active suicide risk, and (c) have worked with JJ staff to identify one caregiver that is willing to participate in the study. The implementation overlay sample includes approximately 203 (out of 810 potential participants with a 25% completion rate) JJ staff (facility staff and probation officers; an average of 22–23 per site) who work directly with youth during residential and/or community re-entry. Out of this sample, approximately 90 JJ staff (an average of 10 per site) are recruited for focus groups.

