### Data analysis plan

For all analyses, an ITT approach is used, where all study participants are included in analyses. For H1 and H2, comparisons of survival curves for each group are performed using SAS PROC PHREG and PROC GLIMMIX using the log rank test with the Sidak multiple-comparison adjustment, with the primary outcome as the dependent variable. Differences between groups on secondary outcomes and change over time in implementation measures (e.g., TBRI use) are examined using repeated measures ANOVAs (SAS 9.4, PROC MIXED), with study site as random effects and condition, time, and interactions as fixed factors. Because SU rates are generally lower among JJ females, sex as a biological variable is examined as a moderator of differences in outcomes using univariate analyses (e.g., chi square, t-tests, ANOVA); when significant, tests of moderation are undertaken as part of all analyses. Putative change mechanisms are investigated as mediators of the Group – Primary Outcome relationship and structural equation modeling (SEM; using Mplus) is used to examine sex differences in mediation. For H3, changes in the outcomes over time are examined using repeated measures ANOVAs (SAS 9.4, PROC MIXED), with study site as random effects and time and time × site interactions as fixed factors. For H1–3, a log rank test is used to assess study dropout; stochastic multiple-imputation provides maximum likelihood estimates, accounts for uncertainty in missing values, and provides unbiased estimates of the treatment effect if data are missing at random.

Qualitative data from focus groups are transcribed and qualitatively coded (in Atlas.ti) by at least 2 research staff. An iterative process of coding and thematic analysis [84] are used to understand routine practices employed, nuances in the use of trauma-informed and child-centered strategies, facility facilitators/barriers to uptake of new interventions, general penetration of TBRI within the facility, and facility interest in sustaining and/or expanding TBRI practices.

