## Discussion

The LeSA project addresses the opioid epidemic by focusing on justice-involved youth at risk for SU and substance use disorders (SUDs). As is well documented, most JJ-involved youth have experimented with using illegal substances and/or developed a SUD prior to entering the JJ system [66] [89] [19] [90] [27]. For this reason, and because youth most often return to the same homes and communities in which they formerly engaged in risky behaviors, the LeSA project is designed to empower existing caregivers—the adults to whom youth are released—with the ability to help prevent opioid and other drug use among JJ youth returning home after secure residential care.

In this project, TBRI is conceptualized as an “indicated” prevention intervention [31] aimed at addressing putative mechanisms underlying risky behavior and SU. Caregivers gain strategies to better support youth after release, strengthen youth-caregiver communication, enhance youth self-regulation, and proactively and effectively identify and address their youth’s needs. TBRI is not only a caregiver intervention but is also a trauma-informed caregiving model that can be applied in any caregiving setting. When the TBRI model is implemented by staff within JJ secure residential settings, strategies used by caregivers at home reinforce the youth’s experiences in the facility (e.g., how to calm themselves when they become dysregulated), resulting in greater continuity as youth transition from one caregiving environment to another. Consistency across multiple contexts within the youth’s broader ecosystem increases the likelihood that behavioral and emotional gains will be sustained [91] [92]. In this regard, the TBRI Caregiver Curriculum has the potential to supplement and extend gains made during residential care.

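### The primary endpoint is opioid initiation, but youth with prior opioid use are not excluded, separated or adjusted for, so what counts as an event for them is left open

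*Protocol article*

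**What the plan says.** All references are to the protocol article.

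- **Outcome (Measurement and outcomes).** "The primary outcome is *days to youth initiation* of non-medical opioid use". No rule says what counts as initiation in a youth who has used opioids before.
- **Hypotheses (Research aims).** H1 and H2 both concern initiating opioid use after discharge. Aim 1(a) is wider: "preventing initiation and/or escalation of opioid use".
- **Eligibility (Study samples and recruitment).** The list opens "Inclusion criteria include youth ages 15–18 at study enrollment who (a) are disposed to community supervision". It then requires care in a secure facility, no active suicide risk and one willing caregiver. No item concerns opioid history.
- **Population (Discussion).** "most JJ-involved youth have experimented with using illegal substances and/or developed a SUD prior to entering the JJ system".
- **Analysis set (Data analysis plan).** "an ITT approach is used, where all study participants are included in analyses". The survival comparison for H1 and H2 is a log-rank test; no stratification or adjustment for prior opioid use is named.
- **Power.** One initiation rate per cohort, 35% (SRP) and 25% (TBRI), is applied to all 360 dyads.
- **Baseline data (Table 4).** Youth complete the TCU DS 5-OS and the HEAL substance use items at baseline and at every follow-up. The Timeline Followback starts at Month 3.

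**The concern.** Endpoint, eligible population and analysis set do not fit together. Escalation is possible only in someone who already uses, so Aim 1(a) presupposes youth for whom first-ever initiation is already past. The primary outcome and H1/H2 make no provision for them.

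Two things are at stake. The first is meaning: a finding that TBRI prevents initiation would not be supported if an unknown part of the events is resumed use. H4 inherits this, because the article measures incremental effectiveness by time to opioid use initiation. The second is validity of H1: Stage 1 youth are compared with later Stage 2 youth, so randomisation does not balance prior opioid use between them. The urn scheme operates only within Stage 2 and balances sex, race and language.

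**Working it through.** **1. The two readings side by side**

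| Meaning of initiation | Youth with prior use | Consequence |
|---|---|---|
| First-ever use | In the risk set, cannot have the event | Observed rates diluted |
| First use after discharge | Can have the event | Resumed use labelled initiation |

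These are alternatives. The wording of H1 and H2 points to the second; the article does not settle it.

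**2. The plan's own power figure**

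Inputs from the Power section: 120 SRP, 240 TBRI, 35% v 25%, α = .05.

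- Expected events: d = 120 × 0.35 + 240 × 0.25 = 42 + 60 = 102.
- HR = ln(0.65)/ln(0.75) = 1.497; ln HR = 0.404.
- Two-sided log-rank power (Schoenfeld) = Φ(√(d × 1/3 × 2/3) × ln HR − 1.96) = Φ(4.761 × 0.404 − 1.96) = Φ(−0.04) = 48.5%.

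The stated 93% is not reproduced (one-sided, the result is 60.9%). That is a separate defect; 48.5% serves here only as the reference value.

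**3. Illustration of the effect on power**

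The share f of prior opioid users is not in the article. Take f = 20% and 40% as assumptions, and read 35%/25% as never-user rates.

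| Handling of prior users | f = 20% | f = 40% |
|---|---|---|
| Kept as never-events: rates | 28%/20% | 21%/15% |
| – events, HR | 81.6, 1.47 | 61.2, 1.45 |
| – power | 37.7% | 27.8% |
| Never-users only: dyads, events | 288, 81.6 | 216, 61.2 |
| – power (HR 1.497) | 40.5% | 31.9% |
| Resumed use counted, at 50% in both cohorts: rates | 38%/30% | 41%/35% |
| – HR | 1.34 | 1.22 |
| – power | 32.2% | 19.6% |

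Worked cell, f = 20% kept as never-events: 0.8 × 35% = 28% and 0.8 × 25% = 20%; d = 33.6 + 48 = 81.6; HR = ln(0.72)/ln(0.80) = 1.47; power = Φ(4.258 × 0.387 − 1.96) = 37.7%.

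The 50% resumption rate, with no TBRI effect on it, is a further assumption. Under it, prior users supply 0.20 × 360 × 0.5 = 36 of 117.6 events (31%) at f = 20%, and 72 of 133.2 (54%) at f = 40%.

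**4. Illustration of bias in H1**

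Suppose TBRI has no effect, never-users have a 35% event rate in both stages, and the share of prior users is 30% in Stage 1 and 20% in Stage 2 (all assumed).

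- First-ever use: 0.7 × 35% = 24.5% (SRP) v 0.8 × 35% = 28% (TBRI). TBRI looks worse by 3.5 points.
- First use after discharge, prior users at 50%: 24.5% + 15% = 39.5% v 28% + 10% = 38%. TBRI looks better by 1.5 points.

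So the same imbalance can push the result in opposite directions, depending on a definition that is not fixed.

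**The case against.** The strongest reply is that the article leans towards the milder reading. H1 and H2 refer to the period after discharge, the stated purpose is prevention after release, and the monthly check-ins ask about any opioid use. On that reading every youth can have the event, and the trial does address whether TBRI prevents opioid use after release. This stands. A reader might infer that the result would answer no clear question, or that it suffers dilution and mixing at once. The documents support neither: the two consequences exclude each other, and under the post-discharge reading the question is answered but mislabelled.

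It can also be said that coding of the risk set belongs in an analysis plan that is not shown, and that the wording of the eligibility list does not mark it as exhaustive. This stands in part. Eligibility of prior users is inferred from the absence of a criterion and from the escalation aim; it is not stated outright. But the mismatch between Aim 1(a) and the primary outcome is in the article itself, as is the rule that everyone is analysed.

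The objection to the figures largely stands. The Discussion speaks of illegal substances in general, so the opioid-specific share is unknown. The 35% and 25% are described as overall rates and may already average over prior users; if so, the reductions in power above would count the same thing twice. A reader might conclude that prior users supply most of the events; that happens only in the more extreme of the two illustrated cases.

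Finally, no difference between stages in prior use has been shown, and each facility is its own control. The bias in H1 is therefore conditional. A facility acting as its own control fixes the site, however, not the mix of youth it holds in successive periods.

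**Conclusion.** The point holds as a defect in the definition of the primary endpoint and in the handling of a strong baseline predictor. Initiation is undefined for youth with prior opioid use, who are not excluded by the listed criteria and are implied by Aim 1(a). For H1 this leaves the comparison of sequential cohorts open to bias if the share of prior users shifts between stages. For H2, where support formats are randomised, prior use is balanced in expectation, and only interpretation and precision are affected.

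The size cannot be fixed from the article. A fall in H1 power from about 49% to 38–28% rests on an assumed 20–40% share of prior users who never have the event, and on reading 35%/25% as never-user rates. It should be taken as an illustration, not an estimate. The conclusion does not depend on it, nor on the 93% figure.

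**What to change.** 1. Define the primary event for all 360 dyads as first non-medical opioid use after discharge, with time counted from discharge.
2. Stratify or adjust the primary model by prior non-medical opioid use, taken from the baseline TCU DS 5-OS and HEAL items. The article does not give their recall windows, so use the longest they provide and state it.
3. Reserve the term initiation for a pre-specified analysis in youth with no prior use at baseline.
4. Align Aim 1(a), H1, H2 and the effectiveness measure in H4 with this wording.
5. Settle this before outcomes are examined by group, since the choice of meaning can change the primary result, and redo the power calculation on the chosen definition.

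The cost is a change of wording and one model term from instruments already given at baseline; the intent-to-treat set is kept whole. The headline claim becomes post-release opioid use, and initiation becomes a smaller subgroup result (288 to 216 dyads under the assumed 20–40%). If TBRI had no effect on resumed use, counting it would lower power, as the last rows of the table show.

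### One normal-theory repeated-measures ANOVA for all secondary outcomes does not suit DERS, whose version changes after baseline, or event outcomes such as overdose and re-arrest

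*Protocol article*

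**What the plan says.** The Data analysis plan gives one between-group method for secondary outcomes: "Differences between groups on secondary outcomes and change over time in implementation measures (e.g., TBRI use) are examined using repeated measures ANOVAs". The model is then specified: these "are examined using repeated measures ANOVAs (SAS 9.4, PROC MIXED), with study site as random effects and condition, time, and interactions as fixed factors".

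The scope is wide. Under Measurement and outcomes, "Secondary outcomes include putative change mechanisms, public health, and public safety outcomes".

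- **DERS.** It is one of three measures that supplement the TCU Adolescent Thinking forms for self-regulation, so it is a putative change mechanism. Table 4 schedules it at baseline and Months 3, 6, 12 and 18. The table note adds: "for baseline the trait version of DERS will be administered and for all follow-ups the state version of DERS will be administered". The Data analysis plan also tests change mechanisms as mediators of the group effect on the primary outcome.
- **Event outcomes.** The list given for the health and safety domain is that they "include opioid-related health, opioid use overdose, use of other illegal substances, recidivism, and SU or MH treatment records". The first item on that list is broken down further into events such as entering treatment, a hospital visit, a diagnosis, an overdose or being given Narcan. Recidivism means re-arrest and re-adjudication and is taken from JJ records, which Table 4 lists as administrative records for Years 2 to 5 with no visit marks.

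No other between-group model is named for these outcomes. PROC GLIMMIX appears for H1 and H2 with the primary outcome. Chi-square appears only in the screening of sex as a moderator.

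**The concern.** A repeated-measures model with a time factor assumes that the same quantity is measured at every level of time. For DERS the first level is one version of the questionnaire and the other four are another. A fall or rise from baseline then mixes real change with the change of version, and so does any mediation analysis built on DERS change. The version switch could also distort the group comparison if the groups start at different levels. SRP and TBRI youth are recruited in successive stages at each site, not randomised against each other, so such a difference is possible.

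For event outcomes, PROC MIXED fits a normal distribution, usually with one residual variance. A yes/no outcome has a variance tied to its rate, and a rate near zero leaves little room below it. Recidivism from administrative records has no scheduled visits, so a visit-based time factor has nothing to attach to, and timing would be lost where dates exist. At stake are the estimates and intervals reported for public health and safety, and the reading of one candidate mediator.

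**Working it through.** The plan gives no figure for this point, so there is none to reproduce. The group sizes of 120 SRP and 240 TBRI come from the Power section. Version shift, scale ratio, baseline imbalance, reliability and event rates are assumptions, because the documents give none of them.

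**DERS**

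1. Let the baseline trait score equal the true level plus error. Let the follow-up state score equal s + k × (true level plus error), where s is the version shift and k the state/trait scale ratio. Assume no true change.
2. Let D be the baseline difference in true level, TBRI minus SRP. The group difference in follow-up minus baseline is kD − D = **(k − 1)D**. The shift s cancels because it moves both groups equally. The bias is zero if D = 0 or k = 1.
3. The time effect does not escape. With D = 0 and levels centred at zero, mean change equals s, although nothing has changed.
4. This was simulated with two time points, 4,000 runs per setting, reliability 0.6 and units of one SD of the true level:

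| s | k | D | Time effect significant | Condition × time significant | (k − 1)D | Simulated bias |
|---|---|---|---|---|---|---|
| −0.3 | 1 | 0 | 99.8% | 4.3% | 0 | −0.003 |
| −0.5 | 1 | 0 | 100% | 4.4% | 0 | 0.002 |
| −0.3 | 1 | 0.3 | 99.8% | 4.8% | 0 | −0.003 |
| −0.3 | 0.6 | 0 | 99.9% | 4.9% | 0 | −0.003 |
| −0.3 | 0.6 | 0.3 | 100% | 18.0% | −0.12 | −0.118 |
| −0.3 | 0.6 | 0.5 | 100% | 41.6% | −0.20 | −0.202 |
| −0.3 | 0.4 | 0.5 | 100% | 70.0% | −0.30 | −0.297 |

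With a version shift the time effect is falsely significant almost always. The interaction goes wrong only when k differs from 1 and D differs from 0 together.

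**Event outcomes**

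1. Take one 0/1 value per youth and a pooled variance, v = (120·p0·q0 + 240·p1·q1)/358, where p0 is the SRP rate, p1 the TBRI rate and q = 1 − p. The model SE is √[v(1/120 + 1/240)] = √(v/80). The true SE is √(p0·q0/120 + p1·q1/240).
2. At 5% versus 1%, v = (120 × 0.0475 + 240 × 0.0099)/358 = 0.02256. The model SE is 0.0168 and the true SE is √(0.000396 + 0.000041) = 0.0209, a ratio of 0.80. With t = 1.967 the approximate coverage is 2Φ(1.967 × 0.803) − 1 = 89%.
3. The half-width for the TBRI rate is 1.967 × √(0.02256/240) = 0.0191, so an observed 1% has a lower limit of about −0.9%.
4. Results from 200,000 simulated trials per setting:

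| SRP rate | TBRI rate | Approximate coverage by formula | Simulated coverage | TBRI interval below zero |
|---|---|---|---|---|
| 5% | 1% | 89% | 87.8% | 94.5% |
| 4% | 1% | 89% | 88.1% | 91.8% |
| 10% | 4% | 92% | 91.1% | 17.4% |

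5. With equal rates in both groups (1, 2, 5 and 30%), the rejection rate was 4.0, 4.1, 4.8 and 5.1%.
6. For two equal arms of 80, the pooled SE² is close to (p0·q0 + p1·q1)/80, which is the true value. The variance mismatch in step 2 therefore comes from the 120:240 split.

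**The case against.** The best defence is that a condensed article states a general method and leaves the handling of individual instruments to the full protocol or SAP. The text does not say which visits form the time factor, nor that DERS change is the mediator, nor how overdose or re-arrest is coded. The version switch is openly disclosed. All of that is fair, so the DERS point is conditional on baseline being a level of time. That is the natural reading of the model next to Table 4, but not the only one. The model itself, however, is stated without any split by outcome type, and none of the natural codings of the event outcomes fits it well.

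Several stronger readings are tempting and are not supported:

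- *That the DERS results are uninterpretable.* Contrasts among follow-up visits all use the state version and are sound. The interaction test held 4.3 to 4.9% error when groups were equal at baseline or the shift was purely additive. The 18 to 70% range needs two assumed conditions at once.
- *That the problem touches H1 or a lead mechanism.* H1 concerns opioid initiation and is analysed by survival methods. DERS is a supplementary measure, and the Table 4 note gives no version change for the TCU forms.
- *That the randomised comparison is compromised.* The three support formats are randomised within site, so only chance imbalance in DERS can enter there.
- *That F-tests on binary outcomes are invalid.* The null error rate was close to nominal in the settings tried.
- *That few events prove the ANOVA wrong.* At assumed rates of 1 to 5%, an arm of 80 expects 80 × 0.01 = 0.8 to 80 × 0.05 = 4 cases. That means low power under any model, including the one proposed here.

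**Conclusion.** The point holds in a limited form. The stated method gives a DERS time effect confounded with questionnaire version if baseline is a level of time, and mediation through DERS change would inherit this. The group contrast is biased by (k − 1) times the baseline imbalance, which matters mainly for SRP versus TBRI. Its size cannot be fixed from the documents, because neither k nor the imbalance is given.

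For event outcomes the method is a poor fit for estimation more than for testing: coverage was about 88 to 91% instead of 95% under assumed low, unequal rates with the 120:240 split, and lower limits for rare events often fell below zero. That calculation uses one observation per youth and a common variance, so it illustrates the mechanism and does not predict this trial's result. Separately, a visit-based time factor does not match recidivism data drawn from administrative records. Only secondary outcomes and one candidate mediator are affected.

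**What to change.** Amend the secondary-outcome sentence in the Data analysis plan, or settle the matter in the SAP if it is not already settled there:

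1. **DERS.** Model the state scores at Months 3, 6, 12 and 18, with the baseline trait score as a covariate and not as a level of time. Report no change from baseline, and define any DERS mediator on state scores.
2. **Binary or count outcomes.** State the coding of each, and use generalized linear mixed models with site as a random effect. PROC GLIMMIX is already named in the plan. Use exact or penalised methods when events are few.
3. **Re-arrest and re-adjudication.** Use time-to-event models from discharge where the records give dates.

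The cost is analysis wording, with no change to data collection. There are two downsides. A DERS change from baseline can no longer be quoted, although the version switch already makes that figure unsound. Adjusting for baseline trait DERS also does not remove all bias from the non-randomised SRP versus TBRI contrast, and the report should say so.
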